### Surgical specimen analysis

Histological analysis of the specimen will include tumor grade according to Edmondson’s scale, tumor size, tumor number, margins, radicality of resection (R0, R1, R2), the existence of portal microthrombosis, the existence of vascular emboles, the existence of perineural invasion, the existence of fibrosis in the adjacent non-tumorous liver parenchyma (F3, F4), the existence of a rupture of the Glisson’s capsule in case of peripheral tumors.

### Follow-up

The inclusion period will last 24 months, allowing the inclusion of 152 patients over that period. The project will finish 90 days after the end of the inclusion period, once the “end of research visit” of the last included patient has been completed. The total study period will therefore correspond to a 27-month period. Two follow-up visits will be scheduled after hospital discharge: at 1 month +/− 7 days (M1) after the surgery, and at 3 months +/− 14 days (M3).

The M1 follow-up visit is performed by the surgeon in charge of the patient and will comprise standard physical examination (including wound examination, measurement of weight and umbilical circumference, heart rate, arterial pressure), biological analyses (INR, prothrombin time, serum total bilirubin, SGOT, SGPT, and creatinine) and a contrast-enhanced abdomino-pelvic CT to asses the existence of ascites and to depict any other postoperative complication. This postoperative 1-month CT scan is in accordance with the standard of care of all five centers involved in the present study, and should not be considered as part of the experiment but as part of the standard follow-up management.

The M3 follow-up visit is performed by either the surgeon or the oncologist/hepatologist in charge of the patient. This visit is also considered as the “end of research visit” and will comprise the same examinations than those in M1.

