### Endpoints and outcome measurements

The primary endpoint will be the presence or absence of postoperative ascites occurring during the postoperative course (within 90 postoperative days). Postoperative ascites will be defined by the existence of ≥500 ml / 24 h of fluid in the drains during at least 3 days, or any ascites requiring an invasive procedure comprising percutaneous puncture or drainage (radiologically or surgically). This definition of ascites of ≥500 ml/24 h is the most common definition of postoperative ascites in the medical literature: several widely reported studies have used that definition [26–31]. Moreover, Azoulay et al. added to this definition the necessity of a 3-day period, which avoids selection bias related to postoperative fluid caused by bleeding, residual lavage or bile leakage [27]. In addition to this definition, we added the need for an invasive procedure as a definition of ascites because some patients may develop ascites after drain removal, or may develop some ascites that is not drained appropriately by the surgical drain, which will require additional invasive management such as puncture or drainage.

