Secondary endpoints are duration and total amount of ascites, postoperative overall 90-day morbidity, the existence and the severity of postoperative liver failure, the existence and the severity of postoperative acute renal failure, postoperative mortality (overall and liver-related), length of stay in intensive care unit, and length of hospital stay. A standardized definition and/or grading system will be considered for all these secondary endpoints as follows: duration of ascites will be defined as the number of days with ascites ≥500 ml/24 h; total amount of ascites will be defined as the total quantity of ascites collected by the drains from surgery to drain removal, associated with the total quantity of ascites collected by radiological puncture or drains if secondary drainage or puncture has been performed; postoperative morbidity will be graded according to the Dindo-Clavien scale [32]; postoperative liver failure will be defined and graded according to the International Study Group of Liver Surgery (ISGLS) definition and grading system [33]; postoperative acute renal failure will be defined according to the “Acute Dialysis Quality Initiative” (ADQI) definition and graded according to the “Risk, Injury, Failure, Loss, End-stage kidney disease” (RIFLE) Scale [34]; postoperative mortality will be defined as any death occurring within 90 postoperative days. Cases of death will be divided into liver failure-related versus liver failure-unrelated deaths.

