### Postoperative care

#### Global postoperative care

After hepatectomy, the patient will stay in an intensive care unit during a short period of 2 to 4 days (for information purposes only, the duration is left at the discretion of the team in charge of the patient) or will return directly to the conventional hospitalization unit. Besides the postoperative infusion of somatostatin (experimental arm) or placebo (control arm), all other postoperative therapies will be standardized for all patients regardless of the arm in which patients are included. In addition, patients will benefit from a standard postoperative monitoring including physical examination (including umbilical circumference, weight, heart rate, arterial pressure, urine out-put) twice a day, standard liver tests and renal blood tests at postoperative day 1, then every 48 h until postoperative day 15 (postoperative days 3, 5, 7, 9, 11, 13, 15) or patient discharge. The tested blood parameters must include: INR, prothrombin time, serum total bilirubin, SGOT, SGPT, and creatinine. Other blood tests may be performed at the physician’s discretion. The glomerular filtration rate will be estimated according to the CKD-EPI formula. A computed tomography will be performed approximately one month after the procedure (+/− 5 days), to assess the presence of subclinical ascites or other intra-abdominal cavity complications.

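### The last visit may fall from about day 76, so up to 14 days of the 90-day window for ascites, morbidity and death may go unobserved

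*Protocol article*

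**What the plan says.** The section Endpoints and outcome measurements ties three outcomes to day 90. For ascites: "The primary endpoint will be the presence or absence of postoperative ascites occurring during the postoperative course (within 90 postoperative days". For death: "postoperative mortality will be defined as any death occurring within 90 postoperative days". The secondary endpoints also include "postoperative overall 90-day morbidity".

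The Follow-up section schedules two visits after discharge: "at 1 month +/− 7 days (M1) after the surgery, and at 3 months +/− 14 days (M3". The second, M3, is also the visit at which the patient's participation in the research ends. Nothing is scheduled after it.

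The same section says of the study as a whole: "The project will finish 90 days after the end of the inclusion period". It adds the condition that the last patient's closing visit has been completed, and derives a total duration of 27 months from 24 months of inclusion.

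The section Sample size and statistical analysis treats follow-up as lasting 90 days. It reports the primary endpoint and the categorical secondary endpoints as counts and percentages, compares the categorical variables by chi-squared or Fisher's exact test, and adds logistic regression for the primary endpoint.

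**The concern.** A 90-day outcome needs observation to day 90. The visit window is symmetric around 3 months, so its early half lets the last planned contact come before the outcome window closes. A patient seen then has followed the protocol fully, yet an event between that visit and day 90 has no planned route into the data.

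The analysis does not absorb the gap. Each outcome is a yes/no proportion, and the article describes no censoring or time-to-event method. Patients seen early and patients seen late would therefore enter the same percentage with different lengths of observation.

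The events exposed are ones that the trial set out to capture. The invasive-procedure limb of the ascites definition was added partly because ascites may appear once the drains are out. Late punctures or drainages, late complications and deaths after discharge all belong to this period.

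**Working it through.** **Inputs from the protocol article**
- Outcome window: 90 postoperative days (Endpoints and outcome measurements).
- Last visit: 3 months, tolerance 14 days either way, end of research (Follow-up).
- Inclusion: 24 months; nominal study end 90 days later; total 27 months (Follow-up).
- Design: 35% against 15%, two-sided 5%, 80% power, 72 per arm (Sample size and statistical analysis).
- Consent is signed the day before surgery (Ethical considerations and written informed consent).

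**1. The plan's own duration.** With a mean month of 30.4375 days, 24 months = 730.5 days. (730.5 + 90) / 30.4375 = 26.96, which rounds to the stated 27 months. The figure reproduces, but only with no tolerance on the last visit.

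**2. Early side of the M3 window.** Earliest visit = 3 months − 14 days.
- 3 months = 90 days: 90 − 14 = day 76. Uncovered: 90 − 76 = 14 days; 14 / 90 = 15.6%.
- Three calendar months run from 89 to 92 days. 89 − 14 = day 75 leaves 15 days (16.7%); 92 − 14 = day 78 leaves 12 days (13.3%).

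**3. Late side of the M3 window.** Latest visit = 3 months + 14 days: 90 + 14 = day 104 (103 to 106 by calendar month). This covers the whole outcome window. For a patient operated on at the close of inclusion, it falls 14 days after the nominal study end (13 to 16 by calendar month, one more if surgery is the day after inclusion).
- (730.5 + 104) / 30.4375 = 27.42 months.
- (730.5 + 107) / 30.4375 = 27.52 months.

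**4. Possible effect on the primary comparison.** The article gives no timing of events, so the share missed, f, is an assumption. It is applied equally to both arms: p1 = 0.35(1 − f), p2 = 0.15(1 − f). With n = 72 per arm and p̄ = (p1 + p2)/2:

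power = Φ{ [ (p1 − p2)√n − 1.96 √(2p̄(1 − p̄)) ] / √( p1(1 − p1) + p2(1 − p2) ) }

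For f = 0: (0.20 × 8.485 − 1.96 × 0.6124) / 0.5958 = 0.834, so power is 79.8%. This agrees with the planned 80%.

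| Share of events missed (assumed) | Power at 72 per arm |
|---|---|
| 0% | 79.8% |
| 1% | 79.2% |
| 2% | 78.7% |
| 5% | 77.0% |
| 15.6% | 70.3% |

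The last row is an outer bound: every patient seen on day 76 and events spread evenly over 90 days. Neither is plausible, because the drain-volume limb of the endpoint can only be met while drains are in place, and their mobilisation starts on day 5 (Abdominal drain).

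**The case against.** **The article is a condensed text.** The full protocol may contain a day-90 call or vital-status check, and its absence from an article is not a fault. That limits the claim to what may go unobserved. It does not remove the point, which rests on a stated rule: the visit that closes participation is allowed before the outcome window ends.

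**The effect on the primary endpoint is small.** This stands. Only a first invasive procedure for ascites between about day 76 and day 90 can be lost. The window is the same in both arms and the trial is double-blind, so no bias between arms is shown.

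**Stronger readings that the document does not support**
- A reader might infer that patients seen early are counted as alive and free of ascites at day 90. The article gives no such rule. It gives no rule for early visits at all.
- A reader might infer that about half of patients lose 7 days on average. That needs visits spread evenly over the window, which nothing in the article supports.
- A reader might infer that the study would close before a late last visit, pushing the last patients into the early half of the window. The Follow-up section also makes the end conditional on completion of the last patient's closing visit. Only the nominal 90 days and 27 months omit the tolerance, and this matters only for patients operated on in about the last two weeks of inclusion.
- A reader might infer a conflict over the month-1 scan. Global postoperative care says "A computed tomography will be performed approximately one month after the procedure", with 5 days either way, while the M1 visit has 7. The narrower window lies inside the wider one, so both can be met.

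**Conclusion.** The point holds in a limited form. A compliant final visit may fall on about day 76, and up to 14 of 90 days (12 to 15 by calendar month, 13% to 17%) may then go unobserved for that patient. This is permitted for any patient but certain for none. How many would be affected cannot be derived from the article.

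The effect on the primary endpoint is probably small and similar in both arms, on the assumption that most ascites arises early. Late complications and deaths share the same gap, and the article gives no figures from which to size it for them. The sample size is not affected. The conclusion rests on there being no contact on or after day 90 other than M3; a check in the full protocol would close the gap. The nominal duration of 27 months is short by up to about half a month, a planning matter on which no estimate depends.

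**What to change.** 1. Set the M3 window to day 90 to day 104 (0/+14 days). Alternatively, keep the present window and add a day-90 telephone or vital-status check for anyone seen earlier.
2. Record ascites procedures, complications and vital status through day 90, with dates, so that events after day 90 found at a late visit are not counted.
3. Restate the nominal study end as the last patient's M3 visit, up to about 104 days after the last surgery, with a total of about 27.5 months in place of 27.

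The cost is protocol wording, the visit calendar, a short call for patients already seen early, and up to two weeks on the study end date. Treatment and the endpoint definitions do not change.

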### Participating centers

All participating centers are required to be experienced in hepatic surgery and management of HCC. Overall, 4 French centers will participate in the study: The Croix-Rousse University Hospital in Lyon, the Pontchaillou University Hospital in Rennes, the Haut-Lévêque University Hospital in Bordeaux, and the Rangueil University Hospital in Toulouse.

### Sample size and statistical analysis

The hypothesis of this phase III study is that the postoperative intravenous infusion of somatostatin during the 6 first postoperative days will reduce the rate of patients developing postoperative ascites. Based on previous published studies, the incidence of postoperative ascites in patients undergoing hepatectomy for HCC is estimated to be 35% (the reported incidence in literature varies between 5 and 56% [26–31], with a median value of 35%, which is consistent with our own experience of 33% postoperative ascites following hepatectomy by laparotomy for HCC at our institution [unpublished data]).

We postulate that we will observe a reduction of the incidence of postoperative ascites from 35% in the control arm to 15% in the experimental arm. In order to demonstrate a 20% difference with an alpha risk of 5% and a power of 80% using a two-tailed hypothesis, 72 patients in each arm will be necessary. Due to the short follow-up period of 90 days in this study, we assume that no more than 1 patient will be lost to follow-up. Additionally, we assume that 5% (*n* = 7) of the included patients will be precluded from surgical resection due to the findings of the surgical exploration (for instance, because of peritoneal carcinomatosis at surgical exploration), and thus will not be evaluable. Therefore, a total of 152 patients will have to be included in this study. To reach this number of patients, a 2-year inclusion period will be necessary.

Patients included in this study will be analyzed on an intent-to-treat basis, and therefore kept in their initial treatment arm, even if the experimental treatment must be interrupted for any reason. The primary endpoint will be expressed in total number of cases in each group and in percentages with 95%-confidence interval. The secondary endpoints’ categorical variables (severity of ascites, postoperative morbidity, postoperative liver failure, postoperative acute renal failure, postoperative mortality) will also be expressed in total number of cases in each group and in percentages with 95%-confidence interval. These categorical variables will be compared between the two study arms using the chi-2 test or the Fisher’s exact test, as appropriate. The secondary endpoints’ continuous variables (duration of ascites, total amount of ascites, length of stay in intensive care unit, length of hospital stay) will be expressed as median values and range, and will be compared using the Mann-Whitney U-test. In order to take account of the potential effects of confounders on the primary endpoint, univariate and multivariate logistic regressions will be performed.

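### Severity grades for liver failure, renal failure and morbidity have only an unordered test, and a severity-of-ascites variable is analysed but never defined

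*Protocol article*

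**What the plan says.** Protocol article, Endpoints and outcome measurements: the secondary endpoints include "the existence and the severity of postoperative liver failure, the existence and the severity of postoperative acute renal failure". Each has an ordered scale. For the liver, "postoperative liver failure will be defined and graded according to the International Study Group of Liver Surgery (ISGLS) definition and grading system"; for the kidney, the RIFLE stages. In addition, "postoperative morbidity will be graded according to the Dindo-Clavien scale". For ascites, the secondary measures in this section are its duration and its total amount.

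Protocol article, Sample size and statistical analysis: the categorical secondary variables are given as "severity of ascites, postoperative morbidity, postoperative liver failure, postoperative acute renal failure, postoperative mortality". They "will also be expressed in total number of cases in each group and in percentages with 95%-confidence interval". The test is fixed: "These categorical variables will be compared between the two study arms using the chi-2 test or the Fisher’s exact test, as appropriate". The Mann-Whitney test is reserved for the continuous variables: duration and amount of ascites, and the two lengths of stay. No rank, trend or ordinal method is named for any grade.

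**The concern.** The two sections do not fit together on severity. One declares it an endpoint on ordered scales; the other supplies only a test that gives the same result however the grades are ordered. On a table with four or more levels, that test spreads its power over every kind of difference between the arms, including differences with no better-or-worse direction. A significant result then does not by itself say that grades became milder.

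These endpoints would show whether less ascites also means less liver failure, renal failure and morbidity. At stake are the efficiency and the interpretability of that secondary evidence. Separately, a severity-of-ascites variable is to be analysed although nothing says how it is graded.

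**Working it through.** **1. The two sections side by side**

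| Variable | Endpoint section | Statistical section |
|---|---|---|
| Liver failure | existence and severity, ISGLS | listed without saying which; chi-2/Fisher |
| Renal failure | existence and severity, RIFLE | same |
| Morbidity | graded, Dindo-Clavien | same |
| Mortality | any death within 90 days (yes/no) | chi-2/Fisher, suitable |
| Severity of ascites | not listed, no grades | chi-2/Fisher |

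**2. The plan's own figure.** The only power statement is for the primary endpoint: 35% versus 15%, two-sided 5%, 80% power, 72 per arm. The normal approximation gives 73 (pooled variance) or 70 (unpooled), and power at 72 per arm is 79.8%. The total is 2 × 72 + 1 + 7 = 152. No power is stated for a graded endpoint, so 72 per arm is used below only as the available size.

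**3. Check that needs no grade distribution.** A signal with 80% power on 1 degree of freedom has noncentrality (1.960 + 0.842)² = 7.85. Spread over k − 1 degrees of freedom for k levels, the same signal has:
- 3 df (4 levels): 64%
- 4 df (5 levels): 60%
- 5 df (6 levels): 56%

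Restoring 80% on 3 df needs noncentrality 10.90, and 10.90 / 7.85 = 1.39, or 39% more patients.

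**4. Simulation under a consistent shift.** The documents give no grade distribution, so the control-arm percentages are assumptions. The shift is proportional odds: at each cut, odds(grade ≤ j) in the somatostatin arm = odds in the control arm / OR. For example, with 60% event-free and OR 0.5, the odds go from 1.5 to 3.0, so 75% are event-free. There are 72 per arm and 200,000 runs per scenario. The tests are Pearson chi-2 on the full table, tie-corrected Mann-Whitney, and chi-2 on any event versus none.

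| Assumed control grades, % | OR | chi-2 on grades | Mann-Whitney | chi-2 on yes/no |
|---|---|---|---|---|
| 60/15/15/10 | 0.5 | 34% | 50% | 48% |
| 60/15/15/10 | 0.4 | 54% | 72% | 71% |
| 40/20/20/10/10 | 0.5 | 38% | 60% | 56% |
| 40/20/20/10/10 | 0.4 | 62% | 83% | 79% |

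The gap between the second and third tests in the first two columns of results is 16 to 22 points. With no effect, both grade tests reject in about 5% of runs.

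**5. Sensitivity to the assumed distribution.** With rare renal failure (85/8/4/3%), the figures are 13% versus 25% at OR 0.5 and about 20% versus 37% at OR 0.4. Chi-2 on grades then has a size of 3.8%. With eight Dindo-Clavien levels (40/12/22/8/6/4/3/5%), they are 29% versus 61% at OR 0.5 and 50% versus 83% at OR 0.4 (20,000 runs).

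**6. Patterns that are not a consistent shift.**
- Equal event rate, milder mix (65/8/14/13% versus 65/22/9/4%): chi-2 72%, Mann-Whitney 10%. The advantage reverses.
- Equal event rate, with both the mildest and the worst grade more frequent in one arm (60/10/25/5% versus 60/20/5/15%): chi-2 rejects in 95% of runs, Mann-Whitney in 5%. Here significance is not evidence of benefit or harm.

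**The case against.** The statistical section never says that grades are what is tested. It names liver failure, renal failure and morbidity without the word severity, reports them as counts and percentages like the binary primary endpoint, and lists them beside mortality. On a yes/no reading, chi-2 is within about 1 to 5 points of the rank test. This stands, and it limits the claim. It does not remove the point: on that reading the declared severity endpoints have no comparison, and if the choice is left open it can be made after the data are seen.

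A reader might infer that the plan forfeits a large share of power, or that a benefit on severity will probably be missed. The documents do not support either. They give no grade distribution and no expected effect, the loss depends on a consistent shift, and it reverses when only the mix of grades changes. At OR 0.4, chi-2 still has 54% and 62% power in the main scenarios, and at OR 0.5 on the four-level scale the rank test itself reaches only 50%.

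The direction of an effect is also not hidden, because counts and percentages with confidence intervals are promised for each arm. A journal article may leave details to a fuller plan, but here a test is named for these variables, so its fit can be judged.

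**Conclusion.** The point holds in a limited form and is minor. Severity on ordered scales is a declared secondary endpoint, and the only test given for these variables ignores order. If grades are compared that way, the cost is about 16 to 22 points of power at 72 per arm. This assumes a proportional-odds shift of 0.4 to 0.5 and the four- and five-level distributions above; the loss is about 12 to 17 points when renal failure is rare and larger on a finer Dindo-Clavien scale. If only presence is compared, the power loss is close to nil and the fault is that severity goes unanalysed.

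A reader might go further and call the planned tests wrong. They are not: they keep their error rate, they suit mortality and presence or absence, and no power was promised for these endpoints. The primary endpoint and the total of 152 are untouched.

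The undefined severity of ascites is a mismatch within the document and rests on no assumption.

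**What to change.** 1. State for each of liver failure, renal failure and morbidity that presence is compared by chi-2 or Fisher. Keep those tests for mortality.
2. Compare the grades with no event as grade 0, by a Mann-Whitney or trend test, or by a proportional-odds model with a common odds ratio and 95% confidence interval. The plan already uses Mann-Whitney elsewhere.
3. Report counts per grade and arm in any case, since an ordinal test has less power when only the mix of grades changes at an equal event rate.
4. Leave mortality as its own endpoint. Coding death as the worst liver or renal grade would redefine endpoints that the article keeps apart.
5. Delete severity of ascites, or tie it to the listed duration and total amount.

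The cost is a few lines of analysis text, settled before unblinding. No change to data collection, sample size or the primary analysis is needed.

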**Fig. 1 Fig1:**
[figure not shown]
Study flow chart

In both arms of the study, patients will undergo a hepatectomy by open approach, with intraoperative measurement of portal vein and inferior vena cava pressures before and after liver resection. All patients will benefit from an abdominal drainage. Randomization will be performed after the abdomen is opened and any contraindication for resection (i.e. peritoneal carcinomatosis) has been precluded. Patients will be randomized in equal proportions in two groups. Patients in the experimental group will receive an intravenous postoperative infusion of somatostatin (Eumedica SA, Manage, Belgium) during 5 days at 6 mg/day, followed by one day at 3 mg/day. Treatment will be stopped at the end of day 6. Patients in the control group will receive a placebo infusion consisting of a daily 50 ml intravenous infusion of 0.9% NaCl during 6 days. No additional postoperative infusion or injection of somatostatin or any analogue of somatostatin will be performed during postoperative course.

In order to allow a double-blind design, preparation of somatostatin or placebo will be performed outside the ward where the patient is located by a pharmacist aware of the randomization results. The surgeons and nurses in charge will thus be unaware of the allocated treatment. Intraoperative management of vascular fluids and postoperative management of ascites will be defined by a common protocol. Abdominal drains will be left in place during at least 4 days and will be mobilized systematically from postoperative day 5 onwards.

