### Randomization

Patients will be randomized during the operative procedure after the abdomen has been opened and the peritoneal cavity explored, precluding any contraindication for surgical resection. For patients in the experimental arm, an intravenous infusion of somatostatin (Eumedica SA, Manage, Belgium) at full-dose (6 mg/24 h) will be started at abdominal closure, and performed during 5 days, followed by a half-dose (3 mg/24 h) infusion during 1 day before it is stopped. Patients in the control arm will receive placebo infusion consisting of 50 ml intravenous infusion of 0.9% NaCl during 6 days.

The randomization will be performed using the stratified block randomization method for each center. A randomization list will be generated for each center and envelopes will be prepared and blinded for allocation during surgery according to consecutive inclusion.

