### End of the surgical procedure

At the end of each procedure, a surgical drain will be placed within the surgical site in order to drain the abdominal cavity and potential postoperative fluids. The modality of drainage utilized will be standardized in each center and will consist of the use of a closed-circuit drain without suction.

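### Randomisation is blocked by centre, but the named tests ignore centre: valid, mildly conservative, and easily aligned with the design

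*Protocol article*

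**What the plan says.** All references are to the protocol article.

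- **Randomization:** "The randomization will be performed using the stratified block randomization method for each center". A separate list is generated per centre, and no other stratification factor is mentioned. The Protocol overview adds: "Patients will be randomized in equal proportions in two groups".
- **Sample size and statistical analysis, categorical endpoints:** "These categorical variables will be compared between the two study arms using the chi-2 test", with Fisher's exact test as the alternative.
- **Same section, continuous endpoints** (ascites duration and volume, intensive care stay, hospital stay): they "will be expressed as median values and range, and will be compared using the Mann-Whitney U-test".
- **Same section, primary endpoint:** univariate and multivariate logistic regressions are planned to allow for confounders. No covariates are listed and centre is not named.
- **Number of centres:** Participating centers states "Overall, 4 French centers will participate in the study" and names four. Follow-up describes the one-month CT scan as "in accordance with the standard of care of all five centers involved in the present study".

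**The concern.** When allocation is balanced within centres, the arms cannot differ much in centre mix. A crude test does not know this. It counts between-centre variation in outcome as noise in the treatment comparison and so uses a null variance that is too large. The actual type I error then falls below the nominal 5%, and some power may be lost compared with a test that conditions on centre.

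The effect is nil if centres have the same outcome distribution and grows as they diverge. The article gives one clear reason to expect divergence on a tested endpoint: for intensive care stay, "the duration is left at the discretion of the team in charge of the patient". For ascites the reason is weaker, as discussed under the objection.

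At stake is a small amount of efficiency on the primary endpoint, possibly more on the stay endpoints, and agreement between design and analysis.

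**Working it through.** **1. The plan's own figure.** Inputs from Sample size and statistical analysis: 35% versus 15%, two-sided alpha 5%, power 80%.

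n per arm = [1.960·√(2·0.25·0.75) + 0.842·√(0.35·0.65 + 0.15·0.85)]² / 0.20² = (1.200 + 0.501)² / 0.04 ≈ 72.4, so 73 (pooled variance, no continuity correction). The unpooled formula gives 70 and the arcsine formula 71. The stated 72 is reproduced within the spread of standard formulas; approximate power at 72 per arm is 79.8%. The total is 144 + 1 + 7 = 152, as stated. The sample size is not in question.

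**2. Why the crude chi-2 is conservative.** With equal centres and 1:1 allocation within each, the null variance of the difference is proportional to the mean of pᵢ(1−pᵢ), which equals p̄(1−p̄) − Var(pᵢ). The crude test uses p̄(1−p̄). With p̄ = 0.35, p̄(1−p̄) = 0.2275.

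- Centre rates 20/30/40/50%: Var = 0.0125; ratio = 1 − 0.0125/0.2275 = 0.945; actual size ≈ 2Φ(−1.96/√0.945) ≈ 4.4%.
- Centre rates 10/25/45/60%: Var = 0.03625; ratio = 0.841; actual size ≈ 2Φ(−1.96/√0.841) ≈ 3.3%.

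**3. Simulation, primary endpoint.** 200,000 replicates; 4 centres, 18 patients per arm in each; a common odds ratio chosen so that the overall rates stay at the planned 35% and 15%. The CMH statistic, without continuity correction, is [Σ(aᵢ − mᵢ/2)]² / Σ[sᵢ²mᵢ(Nᵢ−mᵢ)/(Nᵢ²(Nᵢ−1))], where aᵢ is control events, mᵢ total events, sᵢ patients per arm and Nᵢ = 2sᵢ in centre i. The centre spreads are assumptions.

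| Centre control rates | Type I error, chi-2 | Type I error, CMH | Power, chi-2 | Power, CMH | Difference |
|---|---|---|---|---|---|
| all 35% | 4.8% | about 4.9% | 80.9% | 80.3% | −0.6 |
| 20/30/40/50% | 4.2% | about 4.9% | 81.5% | 82.1% | +0.6 |
| 10/25/45/60% | 3.1% | about 4.9% | 82.5% | 85.2% | +2.7 |

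The type I error column agrees closely with step 2. Moderately unequal centres (22/28/28/22% of patients, rates 20-50%) give much the same: type I error 4.2% versus 4.9%, power 81.4% versus 81.8%.

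**4. Simulation, continuous endpoints.** Same layout, normal outcomes, an assumed treatment effect of 0.47 SD and assumed centre shifts. The between-centre share is the mean squared shift divided by (1 + mean squared shift).

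| Centre shifts (SD) | Between-centre share of variance | Power, Mann-Whitney | Power, van Elteren |
|---|---|---|---|
| none | 0% | 79% | 78% |
| ±0.1, ±0.3 | 0.05/1.05 = 5% | 76% | 78% |
| ±0.25, ±0.75 | 0.3125/1.3125 = 24% | 68% | 78% |

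Repeat runs of this part differ by up to about one point.

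**The case against.** The other side has several good arguments.

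- **Validity is intact.** An unstratified chi-2 after centre-blocked randomisation does not inflate type I error. Preferring CMH is an efficiency choice, and with no centre differences CMH costs about 0.6 points. This stands.
- **Power is not undermined.** A reader might infer that power drops below the planned 80% whenever centres differ. The documents do not support that. The drop appears only if the within-centre odds ratio is fixed at 0.328 while control rates are spread. The overall somatostatin rate then rises from 15% to 15.6% (20-50%) or 16.9% (10-60%), so a smaller effect is being tested. Chi-2 power is then 78.5% and 72.9%, but the same diluted overall rates with no centre differences give 77.9% and 71.5%. The dilution causes the loss. At the planned 35% versus 15%, chi-2 power stays above 80%.
- **Not every analysis ignores centre.** The multivariate logistic regression could include centre; the text simply does not say so. The sentence naming chi-2 and Fisher also follows directly on the list of secondary endpoints, so its application to the primary endpoint is a natural reading but not an explicit one. This limits the point to the tests as named.
- **Drainage is a weak source of centre differences.** "The modality of drainage utilized will be standardized in each center" might suggest that drains differ between centres, but the same sentence fixes one type, closed-circuit without suction, for all. Drain timing and ascites management are also common to all centres. Intensive care duration is the one clearly discretionary item.
- **The stay figures rest on assumed inputs.** Neither the 0.47 SD effect nor the shifts come from the article, and the trial was not sized on these endpoints. The figures show sensitivity and do not forecast a loss.
- **An article leaves detail to the SAP.** This answers any complaint that no interval for the between-arm difference is mentioned: the article gives intervals per arm and does not exclude one for the difference. It does not fully answer the present point, because the article positively names unstratified tests.

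**Conclusion.** The point holds as a modest efficiency and design-consistency improvement. Randomisation is stratified by centre; the named tests are not, and the logistic model does not name centre.

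For the primary endpoint, the crude chi-2 runs at 4.8% down to 3.1% type I error over the assumed spreads. A CMH test would change power by between −0.6 and +2.7 points. For the continuous secondary endpoints the gain ranges from slightly negative to about 10 points at the largest shift tabulated, and it is most plausible for intensive care stay.

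All sizes assume 4 centres of 36 with exact within-centre balance. The centre spreads, and the 0.47 SD effect for continuous endpoints, are assumptions that the article neither supports nor contradicts. Neither the validity of the planned tests nor the sample size of 152 is threatened.

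The four-versus-five centre count is a genuine but minor contradiction. It matters here only because the centres are the strata.

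**What to change.** - **Primary endpoint:** name the centre-stratified CMH test, without continuity correction, and report the Mantel-Haenszel risk difference with its 95% CI. Alternatively, name centre as a prespecified covariate in the logistic model.
- **Continuous secondary endpoints:** replace Mann-Whitney with the van Elteren test stratified by centre.
- **Centre count:** reconcile the Participating centers and Follow-up sections so that the strata are defined.

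The cost is analysis wording only, with no change to sample size or trial conduct. The statistical downside is under one point of power on the primary endpoint if centres turn out not to differ, and about one point for the continuous endpoints. If an existing SAP already adjusts for centre, the published description of the tests should be brought into line with it.
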